### Outcome measures

An overview of all measures can be found in table 2 and full details can be found in online supplemental material 3. Primary and mental health measures will be asked at all timepoints, with the Purrble intervention group also receiving two additional engagement measures throughout deployment. An extended survey will replace the weekly survey at three timepoints, this will include three additional measures to be asked to all participants. All surveys will be distributed via Qualtrics using individualised links for each participant.

**Table 2 T2:** Summary of the outcome measures

Outcome measure	Questions (n)	Type of outcome	Frequency	Scoring	Details of assessment
Primary measure					
Difficulties in Emotion Regulation Scale-8^60^	8	Primary outcome	All timepoints	8–40 (higher=more difficulties)	Difficulties associated with response to situations eliciting negative emotions.
Mental health measures					
Self-Harm Questionnaire (SHQ) screening questions^63^	3	Mental health	All timepoints	Analysed separately	Frequency and risk of self-harm thoughts, suicidal ideation and behaviour.
SHQ additional items^63^	22	Covariate	Once (baseline)	Analysed separately	4 dimensions of self-harm (NSSI, suicide attempts, suicide threats, suicide ideation).
Generalised Anxiety Disorder Questionnaire-7^64^	7	Mental health	All timepoints	0–21 (higher=greater severity)	Presence and severity of generalised anxiety disorder.
Patient Health Questionnaire^65^	9	Mental health	All timepoints	0–27 (higher=greater severity)	Severity of depressive symptoms.
Proximal and mechanistic measures					
Process Model of Emotion Regulation Questionnaire^66^	9	Mechanistic	3 timepoints	2 subscales Average across each subscale, higher=greater endorsement.	Attentional deployment subscales; focus on engagement and disengagement.
State Hope Scale^67^	6	Proximal	3 timepoints	6–48 (higher=greater state hopefulness)	Goal-directed thinking; agency and pathways.
UCLA Loneliness Scale for children^68^	3	Proximal	3 timepoints	3–12 (higher=more loneliness)	Subjective feelings of loneliness.
Engagement measures					
Bespoke Purrble questions^59^	7	Engagement	Deployment	Analysed separately	Purrble use and perceived usefulness.
TWente Engagement with Ehealth Technologies Scale^69^	9	Engagement	Deployment	3 subscales Total score per subscale=greater engagement	Engagement with intervention device; behavioural, cognitive and affective engagements.

Note: UCLA= University of California, Los Angeles; NSSI = Non-Suicidal Self-Injury

These additional measures were selected to explore the association between self-harm and ER (Process Model of Emotion Regulation Questionnaire—PMERQ),^38–41^ perceptions of hope (State Hope Scale—SHS)^13^ and loneliness (3-item University of California, Los Angeles (UCLA) Loneliness Scale),^62^ to further explore the qualitative findings represented in our pilot study.^47^ Our findings have previously indicated that Purrble was used to (1) refocus or distract attention during moments of distress by addressing the physical manifestation of their discomfort (PMERQ) and (2) comfort in moments of loneliness and provide self-soothing mechanisms (UCLA, SHS).^47^

Considering participant burden, young people will be informed of the time to complete each weekly survey (15 min) and the extended survey (22 min) and will be compensated for their time.

### Post deployment interviews

We will collect semistructured interview data from LGBTQ+ young people from up to 40% of the intervention group (n=37) and approximately 20% of the control group (n=17). The interviews will be conducted following the deployment period. We will specifically aim to recruit young people who demonstrated the highest and lowest changes in the outcome data over the trial to explore and understand the potential moderators relating to the intervention and mental health across the trial period.

The semistructured interview will explore the engagement and appropriation of the Purrble device, whether LGBTQ+ young people had felt that this had helped them with their ER, mental health more broadly or self-harmful thoughts, and how Purrble may (or may not) be suitable for other audiences. We will compare these experiences between intervention and control participants, exploring other mechanisms used by LGBTQ+ youth who experience self-harm.

### Hypotheses

#### Primary hypothesis

Across the trial, we hypothesise that access to the Purrble intervention (compared with the waitlist control) will lead to a direct decrease in self-reported difficulties with ER as measured by the primary outcome (DERS8), averaged between three pre-deployment (weeks 1–3) and our final three deployment assessments (weeks 11–13).

#### Secondary hypothesis

Intervention effects will be moderated by engagement with the device, measured by bespoke questions and the TWente Engagement with Ehealth Technologies Scale questionnaire. Secondary outcomes in the Purrble effectiveness trial are: self-harmful thoughts, symptoms of anxiety and symptoms of depression. These three constructs were selected as secondary outcomes based on the high prevalence of these experiences among LGBTQ+ youth^3–8^ and their association with poor ER.^38–41^ The three secondary hypotheses are as listed when compared with waitlist controls:

Engagement with the Purrble intervention will reduce the frequency of self-reported self-harmful thoughts (SHQ).Engagement with the Purrble intervention will reduce the severity of self-reported anxiety symptoms (GAD-7).Engagement with the Purrble intervention will reduce the severity of self-reported depression symptoms (PHQ-9).

### Additional analyses

Additional hypotheses aim to understand the impact of Purrble on relevant proximal and mechanistic outcomes. The following hypotheses will be investigated across the trial:

Greater within-group changes will be seen among intervention group participants, with increasing levels of endorsement for attentional deployment (PMERQ), than among those participants of the control group.There will be a greater increase in state hopefulness (SHS) in the Purrble intervention group than the waitlist control.Participants in the Purrble intervention group will report lower loneliness (UCLA) than those in the waitlist control group.

#### Statistical analyses

Testing the hypothesis that access to the Purrble intervention will lead to a reduction in emotion dysregulation, as measured by the composite primary outcome, will be done using a one-sided t-test.

As exploratory analyses, linear mixed models will be fitted to gain insight into how emotion dysregulation is altered with access to the intervention. In particular, we will regress the weekly outcome score on an indicator for the Purrble condition, a linear time trend and an interaction between the treatment indicator and time to examine differential trends in the two groups. We will adjust for baseline covariates and include participant-level random intercepts and slopes to account for persistent baseline differences between young people as well as person-specific time trends in the outcome. While the outcome is limited to DERS8 scores ranging from 8 to 40, we will model it as continuous data.

For secondary aims, we will use analogous linear mixed models to assess the impact of Purrble on relevant outcomes (cf., hypotheses above), adding baseline DERS8 as another covariate. We will not adjust for multiple comparisons, as these are exploratory aims meant to be generate hypotheses. Similarly, we will also assess the impact of access to Purrble on changes in proximal outcomes, as well as explore whether these appear to moderate changes on primary and secondary outcomes.

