#### Recruitment, randomisation and blinding

LGBTQ+ youth will be recruited to the trial by several strategies. These include: (1) approaching secondary schools and colleges, (2) social media adverts, (3) advertising through stakeholder charities and organisations (eg, Bounce Black, Harmless, King’s College London newsletter) and (4) online platforms (eg, MQ Participate). Those organisations which involve gatekeepers (eg, schools, colleges, charities, organisations) will be emailed by one of the leading researchers offering an introductory meeting to discuss the outline of study, explaining safeguarding protocols and how to share this information with young people. Young LGBTQ+ people will then be able to register their interest in the study, anonymously from gatekeepers. At recruitment, participants will not be blinded to the fact that Purrble was designed to support ER. The information sheet specifies that participants will be asked about mood, self-harm and ER over the course of the study.

Once eligibility is confirmed and young LGBTQ+ people have provided written informed consent (online supplemental material 2), they will be 1:1 randomly assigned to either intervention or waitlist control group, using a computerised algorithm. A stratification procedure will be applied to balance gender identity (transgender and gender diverse youth vs cisgender) across the two arms. The researcher conducting randomisation will be blind to treatment group allocation. However, the leading researcher and other team members who will be conducting safeguarding will be aware of group allocation. Researchers collecting outcome measures will be blinded to group allocation. Participants will be informed about their assigned condition. The intervention group will receive the Purrble before T1 data are collected, with waitlist participants receiving their Purrble devices after the 3-month follow-up data collection. Participants may withdraw at any time, once they have received their Purrble device it is theirs to keep.

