### Power analysis

Sample size was determined based on an a priori power analysis to detect a difference between the two arms when considering the primary outcome measure, DERS8. On the basis of a pilot with LGBTQ+ youth^47^ and other Purrble studies,^50 59^ we expect to see a medium effect size for this measure (d=0.4). This would indicate fewer difficulties with ER among young people who had access to Purrble.

With the anticipated medium effect size, simulations were performed involving a range of fixed and random effects. Simulations involved linearly increasing effect over the study period, and sensitivity analysis was performed over a range of scenarios considering the slope of effect change over time was either fixed or random. The simulation used a one sided t-test (=0.05) and targeted a sample size giving at least 80% power. The statistic to be compared between groups is the change in mean DERS8 Score in the 2 weeks preceding intervention (three assessments in total), to the mean DERS8 assessed at weeks 8, 9 and 10. The averaging over three assessments is intended to reduce the known variance in DERS8 when repeatedly assessed.^60^ Other simulations considered only comparing the change in DERS8 from baseline (week 0) to week 10, comparing the slope of the effect, assessed using simple linear regression. All simulations suggested better than 60% power with 70 participants per arm, with the mean change in DERS8 averaged over three assessments and the comparison of slopes, suggesting >80% power. The sample size of 140 is inflated by 20% to account for dropout rate,^61^ rounding up the total sample to 168.

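### The primary t-test on DERS8 change is valid but leaves out the baseline mean and the gender-identity stratum as covariates; adding both is a nearly free, probably modest, gain in precision

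*Protocol article*

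**What the plan says.** Four places in the protocol article bear on this.

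- **Statistical analyses.** The primary hypothesis, "as measured by the composite primary outcome, will be done using a one-sided t-test". No covariates are attached to that test. Baseline covariates appear only in the linear mixed models for DERS8, which are labelled exploratory, and in the analogous models for secondary aims, where baseline DERS8 is added.
- **Power analysis and Primary hypothesis.** "The statistic to be compared between groups is the change in mean DERS8 Score in the 2 weeks preceding intervention" (three assessments) to the mean of the last three deployment assessments, T8–T10. The sample size was simulated on this statistic: "The simulation used a one sided t-test (=0.05) and targeted a sample size giving at least 80% power".
- **Recruitment, randomisation and blinding.** "A stratification procedure will be applied to balance gender identity (transgender and gender diverse youth vs cisgender) across the two arms".
- **Abstract.** Linear mixed models are said to assess the primary as well as the secondary hypotheses. This does not agree with the Statistical analyses section.

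The primary test is stated outright, so it is a choice the article makes and not a detail left to an unseen analysis plan.

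**The concern.** A t-test on change uses the baseline by subtraction, which amounts to a regression with the baseline coefficient held at 1. Analysis of covariance (ANCOVA) estimates that coefficient and, under randomisation, targets the same treatment effect. Three things follow.

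- **Precision.** When the true coefficient is below 1, subtracting the whole baseline puts avoidable noise into the comparison.
- **Chance imbalance.** If the Purrble arm happens to start worse, part of its later fall is regression to the mean, and the change score counts that part as benefit. The reverse holds if it starts better.
- **Stratification.** When randomisation is balanced on a factor that predicts the analysed outcome, an analysis that omits the factor overstates its standard error and is slightly conservative.

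All three affect the trial's one confirmatory test, and every variable needed to deal with them is already collected.

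**Working it through.** **Inputs from the protocol article.** 70 per arm before inflation, 1:1 allocation, one-sided 0.05, target power of at least 80%, d = 0.4, three assessments averaged at each end, one two-level stratum. **Not given:** the correlation r between the two three-assessment means, their SDs, the variance components, and which SD d refers to (single score, three-assessment mean or change). Values for these are assumed below.

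**1. The plan's own figure.** The article reports more than 80% power for the three-assessment change with 70 per arm. It cannot be reproduced exactly, so two readings of d were tried.
- d in SDs of the change: 0.4 × √(70/2) = 2.366, and Φ(2.366 − 1.645) = 76.5% (exact t: 76.1%).
- d in single-score SDs, effect rising linearly to 0.4 at T10, simulated with ICC 0.5–0.8 and slope SD 0–0.5 (assumed): 89% to 100%, consistent with the stated figure.

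**2. Direction.** Let k be the ratio of final to baseline SD, with baseline variance 1.
- Change score: 1 + k² − 2rk.
- ANCOVA: k²(1 − r²).
- Difference: (1 − rk)², which is never negative.

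So in large samples ANCOVA is never less precise, and the two tie only when the true coefficient rk equals 1. With k = 1 the ratio is (1 − r²)/[2(1 − r)] = (1 + r)/2.

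**3. Plausible r, no random slopes.** For single-score ICC ρ, averaging three scores at each end gives r = ρ/[ρ + (1 − ρ)/3].

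| ρ (assumed) | r | (1 + r)/2 | Variance saved | Power from an assumed 80% |
|---|---|---|---|---|
| 0.5 | 0.75 | 0.875 | 12.5% | 84.4% |
| 0.6 | 0.82 | 0.909 | 9.1% | 83.2% |
| 0.7 | 0.875 | 0.9375 | 6.3% | 82.2% |
| 0.8 | 0.92 | 0.962 | 3.8% | 81.4% |

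The last column is Φ(2.486/√ratio − 1.645), where 2.486 = 1.645 + 0.842.

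**4. With random slopes.** Take slopes independent of the intercept, with SD 0.5 single-score SD, counted in full at the final window. This adds 0.25 to the final variance.
- ρ = 0.5: baseline variance 0.667, final 0.917, covariance 0.5. Change: 0.667 + 0.917 − 1.0 = 0.583. ANCOVA: 0.917 − 0.25/0.667 = 0.542. Ratio 0.93. Here r = 0.64, and (1 + r)/2 would wrongly give 0.82, because the SDs are no longer equal.
- ρ = 0.8: baseline 0.867, final 1.117, covariance 0.8. Change: 0.383. ANCOVA: 1.117 − 0.64/0.867 = 0.378. Ratio 0.987, a saving of about 1%. Power from 80% becomes 80.5%.

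**5. Other SD ratios.** At r = 0.8 the variance ratio is 0.997 for k = 1.2 and 0.64 for k = 0.8. The saving nearly vanishes if the final spread is wider, and is larger if it is narrower.

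**6. Simulation from step 1.** ANCOVA power was 91% to 100% against 89% to 100% for the change score, within about 2 points in each scenario.

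**7. Chance imbalance.** Given a baseline difference D, the change-score estimate is displaced by (1 − β)D, where β is the true coefficient. In steps 3 and 4, β is 0.75 to 0.92, so 8% to 25% of D carries through.

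**8. Stratum.** Let it explain a share R² of the variance of the change (assumed), with d = 0.4 in change SDs. Unadjusted type I error is 1 − Φ(1.645/√(1 − R²)). Power is Φ(0.7216/√(1 − R²)) unadjusted and Φ(2.366/√(1 − R²) − 1.645) adjusted.

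| R² | Type I, unadjusted | Power, unadjusted | Power, adjusted |
|---|---|---|---|
| 1% | 4.9% | 76.6% | 76.8% |
| 5% | 4.6% | 77.0% | 78.3% |
| 10% | 4.1% | 77.7% | 80.2% |

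**The case against.** The planned test is legitimate. It matches the stated hypothesis and the statistic on which the sample size was simulated, and across randomisations it is unbiased. Averaging three assessments at each end is itself a variance-reduction step, and it pushes the true baseline coefficient towards 1, where a change score loses least. A stable difference in DERS8 level between gender-identity groups cancels in the subtraction, so the stratum matters only if it predicts change, and the article gives no evidence that it does. A covariate-adjusted mixed model for DERS8 is also planned, though as exploratory.

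All of this stands. It limits the size of the gain without reversing its direction, and an exploratory model does not improve the confirmatory test.

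A reader might infer more than the documents support:

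- **That the test ignores baseline.** It does not; baseline is subtracted. What is missing is its use as a covariate.
- **That a quarter of the variance is wasted.** A ratio of 0.75, which would lift 80% power to about 89%, needs r = 0.5 with equal SDs. The article gives no r, and none of the scenarios in steps 3 and 4 reaches that saving.
- **That adjustment would make up for any shortfall in the dropout allowance.** That is a separate matter, and the claim would rest on the same unstated correlation and on an assumed starting power.
- **That the result would be biased or the error rate inflated.** The imbalance effect is conditional on the imbalance that occurs, and omitting the stratum makes the test slightly conservative.

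**Conclusion.** The point holds as a free improvement, not as an error that undermines the trial. The direction is firm: in large samples the adjusted analysis is never less precise, and it removes the part of a chance baseline difference that a change score carries into the estimate.

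The size is uncertain and probably modest. For single-score ICCs of 0.5 to 0.8 the variance saving is about 4% to 12% without random slopes, and as little as about 1% with them. From an assumed 80% power that is roughly 0.5 to 4 points. The ICCs, the slope SD and the 80% starting point are assumptions. A final SD smaller than the baseline SD would enlarge the gain, but nothing in the article points to one. The stratum's own contribution is probably small.

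**What to change.** In the Statistical analyses section, make the primary test the arm coefficient in a linear model of mean DERS8 at T8–T10 on arm, mean DERS8 at T(−2)–T0 and gender-identity stratum. The same adjustment inside a longitudinal model would also serve. Report the adjusted difference in DERS8 points with its confidence interval. The unadjusted change-score t-test can stay as a supporting analysis.

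In the same edit, reconcile the abstract with the Statistical analyses section, so that both name the same primary analysis.

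The cost is a sentence of text, to be fixed before outcome data by arm are seen. No new data are needed. The target sample size need not change: two extra coefficients reduce the residual degrees of freedom from 138 to 136 with 140 analysed, which is negligible.

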**Methods and analysis:**

The study is a single-blind, randomised control trial comparing access to the Purrble robot with waitlist control. A total of 168 LGBTQ+ youth aged 16–25 years with current self-harmful ideation will be recruited, all based within the UK. The primary outcome is emotion dysregulation (Difficulties with Emotion Regulation Scale-8) measured weekly across a 13-week period, including three pre-deployment timepoints. Secondary outcomes include self-harm (Self-Harm Questionnaire), anxiety (Generalised Anxiety Disorder-7) and depression (Patient Health Questionnaire-9). We will conduct analyses using linear mixed models to assess primary and secondary hypotheses. Intervention participants will have unlimited access to Purrble over the deployment period, which can be used as much or as little as they like. After all assessments, control participants will receive their Purrble, with all participants keeping the robot after the end of the study. After the study has ended, a subset of participants will be invited to participate in semistructured interviews to explore engagement and appropriation of Purrble, considering the young people’s own views of Purrble as an intervention device.

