## Methods

### Trial design

The study is a two-arm randomised controlled trial comparing an intervention group (Purrble robot) with a waitlist control group. The trial period is across 13 weeks, built of 3 pre-deployment assessments and 10 deployment assessments, using weekly, self-reported, validated surveys hosted by Qualtrics (see table 1). The intervention period will commence once Purrble has been deployed to the intervention group, week 4 (T1).

**Table 1 T1:** Overview of assessment design for both participant groups

Surveys	Pre deployment (weeks 1–3)			Deployment (weeks 4–13)				Follow-up (week 13+)
	T(−2)	T(−1)	T(0)	T1–T4	T5	T6–T9	T10	
Register interest+screening	X							
Consent	X							
Main assessment	X	X		X		X		
Extended assessment			X		X		X	
Qualitative interviews								X

Analyses will be conducted and reported in accordance with the Consolidated Standards of Reporting Trials (57 58), with consideration given to the recommendation of psychological interventions.^52^ Outcomes will be assessed 13 times across a 13-week period, including 3 baseline assessments and 10 weeks of deployment, with Purrble being delivered in time for week 4 (T1).

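### The weekly mixed model, most plainly read, fits one straight line per arm through three pre-deployment and ten deployment weeks, so its arm-by-time slope cannot tell an immediate effect from a growing one

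*Protocol article*

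**What the plan says.** The Trial design section describes a series "built of 3 pre-deployment assessments and 10 deployment assessments", with the device reaching the intervention arm for week 4 (T1). The abstract likewise has DERS8 "measured weekly across a 13-week period, including three pre-deployment timepoints". Under Outcome measures, the primary and mental health scales are asked at every timepoint.

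Under Statistical analyses, the primary hypothesis is tested by a one-sided t-test. An exploratory mixed model then regresses the weekly score "on an indicator for the Purrble condition, a linear time trend and an interaction between the treatment indicator and time". It will adjust for baseline covariates and "include participant-level random intercepts and slopes". For the secondary aims, "we will use analogous linear mixed models to assess the impact of Purrble on relevant outcomes", with baseline DERS8 as a further covariate. These aims too are called exploratory. The section does not say that the model is limited to T1–T10, and it does not say how time is coded.

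**The concern.** The device cannot act before it is delivered, so any device effect on the arm difference has a bend or a jump at T1. A model with one intercept and one slope per arm has no place for either. It spreads the change over all 13 weeks and can put part of it in weeks when nobody had a device. Shifting the time origin does not alter the fitted lines.

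Two things are at stake. First, the model is meant to show how the trends differ between arms, and the Secondary objectives ask whether Purrble stays helpful over an extended period. A slope that looks alike for a constant and a growing effect, and almost vanishes for a fading one, cannot answer that. Second, this is the only analysis described for self-harmful thoughts, GAD-7 and PHQ-9.

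An early effect is plausible on the protocol's own account. The Intervention section describes soothing in under 60 s, and the Introduction reports reduced anxiety and self-harmful thoughts in a 2-week pilot deployment.

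**Working it through.** **The plan's own figure.** The plan gives no number for this model. Its sample size, 140 × 1.20 = 168, reproduces but has no bearing here.

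**Inputs.** Weekly times t = −2, …, 10 (13 points, three before T1) come from Trial design. The model terms come from Statistical analyses. The effect shapes are assumptions, except linear build-up, which the Power analysis section assumes. All shapes are zero up to T0, and D is the maximum effect.

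**Method.** With complete, balanced data and random intercepts and slopes, the fixed-effect arm difference equals the least-squares line through the true weekly arm differences δ(t).

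- Mean of t = 4; Sxx = Σ(t − 4)² = 182.
- Slope b = Σ(t − 4)δ(t) / 182.
- Fitted difference at t = mean(δ) + b(t − 4).
- The T8–T10 mean is the fit at t = 9 and the pre-deployment mean is the fit at t = −1, so the fitted late-minus-pre change is 10b.

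**Step: δ = D from T1.** Σ(t − 4) over T1–T10 is 55 − 40 = 15, so b = 15/182 = 0.082D. The mean is 10/13 = 0.769D.

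**Linear build-up: δ = Dt/10.** Σ(t − 4)t/10 = (385 − 220)/10 = 16.5, so b = 16.5/182 = 0.091D. The true slope during deployment is 0.100D. The mean is 5.5/13 = 0.423D.

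**Rise and fade: D/3, 2D/3 and D at T1–T3, then falling by D/7 per week to 0 at T10.** Σ(t − 4)δ = −3.333 + 5 = 1.667, so b = 1.667/182 = 0.009D. The mean is 5/13 = 0.385D.

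| Shape | Slope per week | Fit at T0 (truth 0) | Fit at T10 (truth) | T8–T10 (truth) | Late minus pre (truth) |
|---|---|---|---|---|---|
| Step | 0.082D | 0.44D | 1.26D (1.00D) | 1.18D (1.00D) | 0.82D (1.00D) |
| Linear build-up | 0.091D | 0.06D | 0.97D (1.00D) | 0.88D (0.90D) | 0.91D (0.90D) |
| Rise and fade | 0.009D | 0.35D | 0.44D (0) | 0.43D (0.14D) | 0.09D (0.14D) |

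At the planning effect of d = 0.4, the step case gives 0.44 × 0.4 = 0.18 SD at T0 and 1.26 × 0.4 = 0.51 SD at T10.

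**Check by simulation.** Mixed models fitted to simulated data (70 per arm, 40 replicates, effect 0.40 SD) gave mean slopes of 0.036 for the build-up and 0.034 for the step. For an effect that falls linearly from T1 to zero the mean slope was −0.003. The projections are 0.036, 0.033 and −0.004. Some fits gave convergence warnings, but the mean slopes agree.

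**With the change point.** A model with no arm difference before T1 and a step plus slope from T1 recovers the step, the linear build-up and the linear fade exactly. It does not recover the rise and fade: it gives 0.253D over T8–T10 against a true 0.143D. Categorical week does not have this limit.

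**The case against.** - **The rows are inferred.** The article does not say in so many words that T(−2) to T0 enter the outcome vector. If the model uses T1–T10 only, or holds time at zero until deployment, most of the problem goes. This stands as a limit. A reader might take the baseline DERS8 covariate in the secondary models as proof that pre-deployment scores stay in the DERS8 outcome. It is not: that sentence concerns other outcomes, and the DERS8 model already has unspecified baseline covariates. All 13 weeks is the plain reading because the weekly series is defined that way and no restriction is given.
- **Randomisation does not secure a zero arm difference before T1.** A reader might infer that it does, and that the free arm term is itself an error. But participants are told their arm, no delay is stated, and consent is placed at T(−2). Anticipation or disappointment could separate self-reports before delivery. This stands and shapes the fix.
- **The effect shape is assumed.** The Power analysis assumes linear build-up, under which the model does well. This stands. The large errors need another shape, although the protocol's own account makes an early effect plausible.
- **The model does not report nil for a fading effect.** Only the slope is near zero; the same fit still shows 0.43D over T8–T10. This stands. That figure overstates the true 0.14D.
- **The analyses are exploratory.** The protocol claims only to examine differential trends and does not promise an effect per week of access. This stands and limits the weight of the point. It does not remove it, because the trend is exactly what the slope misdescribes.

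**Conclusion.** The point holds for the exploratory DERS8 model and for the weekly secondary outcomes, on the plain reading that all 13 weeks enter the model. The slope hardly differs between a constant effect (0.082D per week) and a growing one (0.091D), and it nearly vanishes for a rise and fade (0.009D). For a step, the change from pre-deployment to T8–T10 comes out 18% low. Under linear build-up the slope is about 9% low (0.091D against 0.100D) and the T8–T10 difference under 3% low (0.876D against 0.900D).

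The figures are exact for balanced data; dropout would shift them. They do not concern the proximal measures taken at three timepoints.

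A reader might conclude that the trial's main result is at risk. The documents do not support that: the primary t-test compares pre-deployment and final three-week means and does not use this model. The abstract does assign mixed models to the primary hypothesis as well, but that is a separate inconsistency with the Statistical analyses section.

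**What to change.** State which weeks enter the model and how time is coded. Then model the weekly outcomes with categorical week by arm. A simpler form is an arm-by-deployment step plus arm by weeks since deployment, accepting some misfit if the effect curves during deployment.

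Report the arm difference in change from the pre-deployment mean to the T8–T10 mean. This matches the contrast in the Primary hypothesis.

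Constrain the pre-deployment means to be equal only if allocation is not disclosed before T0. Otherwise keep a free pre-deployment arm term, or adjust for the outcome's own pre-deployment mean.

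No new data are needed. The step-plus-slope form costs one or two extra parameters. Categorical week by arm has 13 × 2 = 26 means in place of four fixed effects, before covariates. If the effect really is linear, the estimate will be slightly less precise.
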